## Abstract

**Background:**

Displaced victims of interpersonal violence, such as refugees, asylum seekers, and victims of sexual exploitation, are growing in numbers and are often suffering from a post-traumatic stress disorder (PTSD). At the same time, these victims are known to benefit less from trauma-focused therapy (TFT) and to be less compliant to treatment. The objective of this paper is to describe the rationale and research protocol of an ongoing trial that aims to evaluate different variables that might influence the feasibility of TFT for the study population. Specifically, perceived daily stress, emotion regulation, and mood are investigated as predictors of change in PTSD symptoms during a trauma-focused therapy (narrative exposure therapy (NET)). The feasibility of administering measures tapping these constructs repeatedly during treatment will also be evaluated.

**Methods/design:**

Using an observational treatment design, 80 displaced victims of interpersonal violence will be measured before, during, and after partaking in NET. Several questionnaires tapping PTSD plus the aforementioned possible predictors of PTSD change will be administered: Post-traumatic Stress Disorder Checklist-5, Perceived Stress Scale, Difficulties in Emotion Regulation Scale-18 (pre-test, post-test, and follow-up),subscale impulsivity of the Difficulties in Emotion Regulation Scale-18, Perceived Stress Scale short version, Primary Care Post-traumatic Stress Disorder and a single Mood item (each session). Multilevel modelling will be used to examine the relation between the possible predictors and treatment outcome.

**Discussion:**

The present study is the first to examine the interplay of facilitating and interfering factors possibly impacting treatment feasibility and effectiveness in displaced victims of interpersonal violence with PTSD receiving NET, using repeated measures. The current study can help to improve future treatment based on individual characteristics.

**Trial registration:**

Netherlands Trial Register: NTR7353, retrospectively registered. Date of registration: July 11, 2018.

## Background

Worldwide, there is an increase in the number of victims of interpersonal violence who are forced to leave their home country [1]. When entering a host country, these displaced persons are usually referred to as either ‘refugees’, ‘asylum seekers’, ‘trafficked human beings’, ‘illegal immigrants’ or ‘undocumented people’, depending on their trauma background and legal status. Mostly these groups overlap in their experience of forced migration, their marginalized social position, and the challenges they encounter. In this paper, we will therefore collectively refer to all such groups as ‘displaced people’.

As a result of assorted traumatic events, like war- and conflict-related violence, sexual violence and exploitation, many of these displaced people suffer from a post-traumatic stress disorder (PTSD) [2–5]. PTSD symptoms cause a great burden, render people unable to engage in daily activities and put them at risk for re-victimization [6]. Displaced people suffering from PTSD could therefore benefit from trauma-focused therapy (TFT). TFT is a psychological intervention aiming to decrease PTSD symptoms by fostering the processing of traumatic memories.

Scientific research into TFT for displaced people is scarce. Studies into TFT for non-refugee traumatized populations show higher effects (*d* = 1.08–1.40) [7], than for refugee populations (*g* = .25–1.01) [8]. Moreover, the feasibility of evidence-based therapies within the refugee population is complicated by post-migration obstacles [9] which can result in low treatment compliance and completion levels. Most likely, the primary focus on PTSD fails to address the broader challenges faced by displaced people [10]. Therefore, more insight is needed into factors affecting treatment response during TFT and conditions for recovery. Identifying factors that undermine the feasibility of TFT for displaced people may help to refine the timing and focus of interventions, and thus improve treatment response.

One key factor that potentially undermines the feasibility of treatment is daily stressors, given their proven association with PTSD symptoms [11–13]. Ongoing daily stressors arising from the immigration process, loss of social network, and impaired functioning resulting from PTSD symptoms negatively impact mental health among the study population [13–16]. The burden caused by ongoing daily stressors may impact one’s cognitive functioning in several ways [17]. For example, by occupying the working memory [18], and thereby reducing the cognitive resources needed to process traumatic events.

While there is evidence for the negative impact of daily stressors and perceived daily stress on treatment for displaced populations, the few present studies have yielded ambiguous results. One study affirmed the negative impact of lack of social support, a daily stressor, when present at the start of treatment on treatment outcome [19]. However, a study where clinician-rated daily stressors during treatment could not establish such an impact on treatment [20]. These limited and contradictive findings illustrate the need for more rigorous research on the relation between daily stressors and treatment response within the study population. No study to date has explored the impact of experienced daily stressors while taking part in TFT in the study population.

Another main factor likely to affect the feasibility of TFT for displaced people is emotion regulation, such as insight into, control over, and awareness of one’s emotions (e.g., [21, 22]). Several studies have indicated that emotion dysregulation mediates between traumatic events and the development of PTSD in different groups (e.g., [23]), including traumatized refugees [24]. Emotion dysregulation has been identified as a consequence of trauma and emotional impulsivity in particular as a predictor of future (re)victimization [25, 26]. For TFT to be feasibly applied, a person must be able to stay within a dynamic ‘window of tolerance’, a range of affect that can be regulated at that point in time [27]. Consequently, it is expected that the level of emotion regulation at baseline and improved control over one’s emotions during treatment are both prerequisites for reducing PTSD symptoms [28]. No study to date has looked into the interplay between emotion regulation and PTSD symptoms while taking part in TFT in the study population.

A final main factor that may affect treatment feasibility is depressed mood, which can be measured as a proxy for depression [29]. Among resettled refugees, the comorbidity rate for PTSD with depression is 44%; for depression with PTSD, it is 71% [2]. Previous research on TFT shows that higher baseline levels of depression predict poorer treatment response in displaced individuals [30] and therewith undermine the feasibility of treatment. Meanwhile, TFT has proven effectiveness in reducing symptoms of depression in the study population [31]. Yet, insight in the interaction between depressed mood and PTSD during treatment is currently lacking.

In an umbrella review of prevalence and intervention studies on common mental disorders in asylum seekers and refugees, Turrini et al. [32] found that narrative exposure therapy (NET) was the best-supported TFT for reducing PTSD symptoms. In a meta-analysis of NET [33], it was found that NET is effective in reducing PTSD and depression symptoms across diverse, predominantly war-affected refugee populations [34]. Since it is a first-choice treatment for the study population, NET was chosen as the TFT applied in the present study [33].

As outlined above, several factors (e.g. PTSD, perceived daily stress, emotion dysregulation and mood) tend to impact treatment feasibility. However, their interplay during TFT has not yet been examined. Insight in the feasibility of measuring this interplay in a diverse group of displaced individuals following NET is yet to be established. To best of our knowledge, there are no prior treatment studies for which weekly repeated measures have been carried out within the target population. Additionally, the practical execution of examining the interrelatedness between different parameters (e.g. PTSD, perceived daily stress, emotion dysregulation and mood) is based on questionnaires that are partly adapted for the current study (see ‘Methods’ section). Consequently, their feasibility within the target population has not been objectified yet.

In the present paper, the feasibility, rationale and protocol of an ongoing trial are described. Specifically, we aim to identify relevant predictors of PTSD symptom change during and after NET in 80 displaced victims of interpersonal violence. The primary hypotheses of the study are (1) it is feasible to administer highly repeated measures, within a diverse group of displaced persons. (2) High perceived daily stress, emotion dysregulation, and low mood at baseline and during NET predict higher drop-out, higher no-show and poorer treatment response of NET (i.e. less PTSD symptom reduction), thus undermining the feasibility of NET; (3) Reduction in perceived daily stress and improvement in emotion regulation and mood during NET are associated with concurrent reductions in PTSD symptoms during NET; (4) Change in perceived daily stress, emotion dysregulation, and mood during NET predict subsequent changes in PTSD symptoms at later stages of NET. Furthermore, the study aims to establish whether NET contributes to positive aspects of mental health.

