## Methods

This study follows a repeated measures observational design with baseline assessments, repeated measures over the course of treatment and post-treatment assessments. Twelve to sixteen sessions of NET will be provided to all patients included in the study. Various questionnaires will be administered at baseline (T0, pre-treatment), 1 week after NET completion (T1, post-treatment) and 6 weeks after NET completion (T2, follow-up). In addition, assessments to measure potential processes of change will be performed at the start of each NET session. See Fig. 1 for a detailed overview of the planned design and administered measures.

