### Participants

The study will take place at an outpatient clinic specialized in mental health care for refugees, asylum seekers, victims of sexual exploitation and otherwise traumatized populations in the Capital region in the Netherlands. The study aims to include 80 participants, in order to detect medium to small effect sizes [35]. Patients are referred to the clinic by a general practitioner or by a partnering social welfare organization. Patients’ background/nationality is diverse; most originate from West Africa, the Middle East and Eastern Europe. Their legal status varies from having obtained a residence permit or even Dutch citizenship to illegal residence in the country, and they may reside in asylum seekers centres, specialized shelters for victims of sexual exploitation, governmental shelters for illegal persons or live independently.

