#### Recruitment

This is an ongoing treatment trial. The enrolment period is planned to run for 2.5 years from February 2018 to January 2021. Following multi-disciplinary clinical assessment and evaluation, the diagnosis and treatment indication will be discussed with patients. Those who are eligible for enrolment will be informed about the study and will be invited to participate. This eligibility will be considered as broadly as possible within the inclusion criteria to allow for a representative sample of displaced victims of interpersonal violence. Information about the study aims and objectives, guarantee of anonymization of data and the fact that participants are free to terminate participation at any moment will be given orally and provided on paper through an information leaflet. After, intake patients are placed on a waiting list for NET, ranging from 1 to 4 months. When patients from the waiting list are invited to start NET, they will once again be informed about the study orally and on paper. Patients will be asked to consider participation over a minimum period of 3 days. Afterwards, they will be contacted by phone or face-to face and given ample opportunity to ask additional questions. If they indicate willingness to participate in the study, an appointment is made to sign informed consent and conduct the baseline assessment (T0). Participants are invited to bring someone they trust to this meeting. Participants will be receiving a voucher of 10 euros after the follow-up measurement. If after the first year the aspired total number of participants seems unachievable, prolongation of the enrolment period and multicentre options will be explored after consultation with the involved medical ethical committee.

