#### Questionnaire on Process of Recovery Short Version–15

The QPR is a 5-point scale (0-4), self-report questionnaire that probes people’s recovery and meaningful aspects in the recovery process (e.g., ‘I feel able to take chances in life.’). The QPR-15 consists of 15 items. Mean scores will be calculated, ranging from 0 to 4. The questionnaire has good psychometric properties, and has proven to be associated with quality of life, empowerment, and psychological wellbeing [45]. Administration of the questionnaire lasts approximately 20 minutes. The questionnaire has been selected because it represents psychological wellbeing beyond the scope of mental health symptoms. The QPR is reliable and valid, and has proven to be associated with quality of life, empowerment and psychological wellbeing [45].

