## Discussion

Among the growing number of forcibly displaced people worldwide, many are suffering from trauma-related mental health problems. As psychological treatments for displaced persons with PTSD appear to be less successful than for other populations, insight is needed in factors that affect the feasibility of these treatments. However, relevant research is lacking. The ongoing trial presented in this paper is the first to examine the interplay of factors for feasibility and effectiveness of in displaced victims of interpersonal violence receiving NET. More specifically, the impact of perceived daily stress, emotion dysregulation, and disturbed mood on PTSD symptom changes during TFT are examined.

The theoretical basis of NET has been well documented, and its effectiveness has been examined in various studies and contexts [33, 34, 36]. Yet, specific factors contributing to positive outcomes or constraining its feasibility are largely unidentified. In the current study, repeated measures will identify various constructs relevant for treatment feasibility and response of NET. Since, to our knowledge, this is the first study to use repeated measures within the target population, findings will additionally provide insight into the feasibility of this method for displaced populations.

As the method requires only minor adaptations to usual treatment proceedings and follows an observational design, participants can be included that might have to be excluded in more complex designs [52]. This allows for conclusions based on a sample representing the intended population with high external validity, which is exceptional for this specific group [53]. Although our design favours generalizability of the results, it may reduce the internal validity of the study; for instance, the present design does not allow for the examination of the extent to which observed changes in PTSD can be attributed to NET, but to factors such as natural recovery, bias or confounders. However, as we aim to study factors promoting or constraining treatment feasibility, a naturalistic design is the most ethical, feasible and time-efficient design to obtain answers to our research questions. Besides, the reduced internal validity is partially addressed by limiting the possibly confounding role of concurrent treatment.

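### The additional aim of establishing NET's contribution to positive mental health cannot be answered by a single-group design without a comparator

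*Protocol article*

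**What the plan says.** The last sentence of the Background states, in addition to hypotheses 1 to 4, that "the study aims to establish whether NET contributes to positive aspects of mental health".

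The opening of Methods gives the design: "This study follows a repeated measures observational design with baseline assessments, repeated measures over the course of treatment and post-treatment assessments". It continues: "Twelve to sixteen sessions of NET will be provided to all patients included in the study". Assessments are at T0 (before treatment), T1 (one week after completing NET) and T2 (six weeks after completing it).

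Under Recruitment, "intake patients are placed on a waiting list for NET, ranging from 1 to 4 months". Consent and T0 are arranged only once a patient has been invited to start NET.

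The QPR-15 was chosen because "it represents psychological wellbeing beyond the scope of mental health symptoms". It is the listed instrument that fits the additional aim, although the article does not link the two explicitly.

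In the Discussion the authors accept that "the present design does not allow for the examination of the extent to which observed changes in PTSD can be attributed to NET". They name confounding, bias and natural recovery as rival explanations, and say that restricting concurrent treatment deals with this in part.

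**The concern.** Asking whether NET contributes to something is asking how participants would have fared without it. The study observes no one without NET, and it does not observe the same people over a period before NET. A change in QPR-15 from T0 to T1 or T2 therefore combines any effect of NET with everything else that changes over those weeks.

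The Discussion recognises this for PTSD symptoms, but the aim in the Background is left in causal form. At stake is the conclusion the trial may draw on wellbeing. A pre-post rise in QPR-15 could be read as meeting the aim as worded, and a flat or falling score could be read as showing no contribution. Neither reading would be supported.

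**Working it through.** The article states no figure for this aim, so there is none to reproduce. The point is one of identification and is settled by comparing sections. The arithmetic in step 5 is an illustration only.

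**1. Is there a concurrent comparator?** No. Methods gives NET to all included patients, and no control arm or external benchmark is described.

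**2. Is there a within-person comparator?** No. A wait of 1 to 4 months precedes NET, but T0 comes at its end. Change during the wait is not measured.

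**3. How long is the uncontrolled interval?** The Intervention section gives 12 to 16 sessions, weekly or twice a week. With no missed sessions the course lasts from 12/2 = 6 weeks to 16/1 = 16 weeks. T1 then falls about 7 to 17 weeks after the start of NET (adding 1), and T2 about 12 to 22 weeks after it (adding 6). There is time for change unrelated to NET.

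**4. Does the article close the gap elsewhere?** Once NET starts, other modules are ruled out except in acute crisis, and no new medication is begun. Medication started earlier may continue. This limits one source of confounding. It does not remove natural recovery, which the Discussion itself lists. The Discussion's limitation names PTSD, but its cause is the uncontrolled design, and that cause is the same for the QPR-15.

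**5. Illustration.** Inputs:
- n = 80 pairs, the planned sample, taken as complete.
- n = 60 pairs, an assumed number of completers, because the article gives no dropout rate.
- A two-sided 5% paired t-test, which is an assumption; the article specifies no test for this aim.
- A true NET effect of zero.
- A mean change not due to NET of d standard deviations of the differences. The article gives no value, so a range is shown.

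The probability of significance is P(|T| > c), where T is noncentral t with n − 1 degrees of freedom and noncentrality d√n, and c is the 97.5% point of the central t distribution. For example, d = 0.3 and n = 80 give 0.3 × √80 = 2.68.

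| Assumed drift d | d√80 | P, 80 pairs | d√60 | P, 60 pairs |
|---|---|---|---|---|
| 0 | 0 | 0.050 | 0 | 0.050 |
| 0.1 | 0.89 | 0.143 | 0.77 | 0.119 |
| 0.2 | 1.79 | 0.424 | 1.55 | 0.332 |
| 0.3 | 2.68 | 0.755 | 2.32 | 0.628 |
| 0.4 | 3.58 | 0.942 | 3.10 | 0.862 |
| 0.5 | 4.47 | 0.993 | 3.87 | 0.968 |

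For any non-zero drift, the larger sample makes a significant result more likely although NET does nothing. More patients give a more precise estimate of the wrong quantity.

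**The case against.** The strongest reply is that the limitation is disclosed and the aim is peripheral. The sentence follows four primary hypotheses on feasibility and prediction, and none of them depends on it. The Discussion states the attribution problem openly and defends the naturalistic design. Co-interventions are restricted during NET.

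Most of this stands and limits the point. It does not rescue the aim. The Discussion defends the design as suited to studying what helps or hinders treatment feasibility, which is not NET's own contribution. No section narrows the aim to a description of change.

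Several stronger readings are tempting and are not supported:

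- **That the article itself says QPR-15 change cannot be attributed to NET.** Its sentence concerns PTSD. The extension is an inference, though a direct one.
- **That the QPR-15 analysis is missing.** This is a journal article, and an analysis for an additional aim may sit in the full plan. In any case, no model fitted to single-group pre-post data can by itself separate NET from time.
- **That all other influences would raise the score.** The Background says that stressors arising from immigration harm mental health, so such events could hide a benefit as easily as mimic one. Regression to the mean is not shown either: entry rests on a PTSD diagnosis at intake, with no cut-off on the QPR-15 or on any T0 score.
- **That unrestricted other care runs alongside NET.** That freedom applies to the waiting period before T0, so only carry-over could matter.
- **That the Statistical analysis section's wording about predictor change leading to PTSD change falls with this point.** That is a separate question about predictors, approached through temporal precedence, and the missing NET comparator does not decide it.

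**Conclusion.** The point holds for the additional aim only. As worded, it asks for NET's contribution to positive mental health, and the described design cannot supply it. The basis is what the article states: NET for all, no comparator, T0 after the wait, and an admitted attribution limit for PTSD whose cause applies equally to the QPR-15.

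The conclusion needs no assumption about power or drift. It does take the QPR-15 as the measure serving this aim, given at T0, T1 and T2; the assessment figure is not available to confirm this. The size depends wholly on the assumed drift. From 0.1 to 0.4, the chance of a significant change with no NET effect runs from 0.14 to 0.94 with 80 pairs and from 0.12 to 0.86 with 60. A reader might take the value of about 0.75 at a drift of 0.3 as a property of this trial. It is not, because the documents give no drift and state no such test.

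Hypotheses 1 to 4 are unaffected. The sentence should nevertheless be changed, because it determines what may be concluded about wellbeing.

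**What to change.** Reword the aim to: *describe change in recovery (QPR-15) from T0 to T1 and T2 among patients receiving NET*. Report the result as uncontrolled change that is not attributed to NET. Extend the Discussion's limitation so that it names the QPR-15 as well as PTSD.

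The change needs no new data and does not alter the assessments. The article says that no analysis has yet been performed, so the wording can be settled before results are known. The cost is a weaker claim for this aim: the trial could report how recovery scores changed in patients receiving NET, but not that NET brought the change about.
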